# Evaluating the effect and mechanism of upper limb motor function recovery induced by immersive virtual-reality-based rehabilitation for subacute stroke subjects: study protocol for a randomized controlled trial

**DOI:** 10.1186/s13063-019-3177-y

**Published:** 2019-02-06

**Keywords:** Immersive virtual reality training, Stroke, Upper extremity, Magnetic resonance imaging, Randomized controlled trial, Brain mechanism

## Abstract

**Background:**

There is compelling evidence of beneficial effects of non-immersive virtual reality (VR)-based intervention in the rehabilitation of patients with stroke, whereby patients experience both the real world and the virtual environment. However, to date, research on immersive VR-based rehabilitation is minimal. This study aims to design a randomized controlled trial to assess the effectiveness of immersive VR-based upper extremity rehabilitation in patients with subacute stroke and explore the underlying brain mechanisms of immersive VR-based rehabilitation.

**Methods:**

Subjects (*n* = 60) with subacute stroke (defined as more than 1 week and less than 12 weeks after stroke onset) will be recruited to participate in a single-blinded, randomized controlled trial. Subjects will be randomized 1:1 to either (1) an experimental intervention group, or (2) a conventional group (control). Over a 3-week time period immediately following baseline assessments and randomization, subjects in the experimental group will receive both immersive VR and conventional rehabilitation, while those in the control group will receive conventional rehabilitation only. During the rehabilitation period and over the following 12 weeks, upper extremity function, cognitive function, mental status, and daily living activity performance will be evaluated in the form of questionnaires. To trace brain reorganization in which upper extremity functions previously performed by ischemic-related brain areas are assumed by other brain areas, subjects will have brain scans immediately following enrollment but before randomization, immediately following the conclusion of rehabilitation, and 12 weeks after rehabilitation has concluded.

**Discussion:**

Effectiveness is assessed by evaluating motor improvement using the arm motor section of the Fugl-Meyer assessment. The study utilizes a cutting-edge brain neuroimaging approach to longitudinally trace the effectiveness of both VR-based and conventional training on stroke rehabilitation, which will hopefully describe the effects of the brain mechanisms of the intervention on recovery from stroke. Findings from the trial will greatly contribute to evidence on the use of immersive-VR-based training for stroke rehabilitation.

**Trial registration:**

ClinicalTrials.gov, NCT03086889. Registered on March 22, 2017.

## Background

Stroke is a major cause of death and long-term disability across the globe [1, 2] and its incidence is decreasing in the USA [3] but rising in China [4]. A common disabling consequence of stroke is upper limb dysfunction [5], which significantly affects patients’ activities of daily life. Therefore, one of the main goals of stroke rehabilitation is to improve upper limb function. Conventional rehabilitation techniques are effective in improving upper limb function but are resource-intensive and costly, often requiring specialized facilities not always widely available [6–8]. Moreover, in order to elicit significant improvement for stroke survivors, conventional upper limb rehabilitation usually requires 2–3 h of training per day for over 6 weeks [9], which is monotonous, confidence and interest draining for patients, and taxing on therapists. Therefore, it is imperative to find an alternative to overcome these drawbacks.

Virtual reality (VR)-based training might be one of the solutions. VR systems are classified as either immersive or non-immersive VR systems [10, 11]. In contrast to non-immersive VR systems, in which users experience both the real world and the virtual environment [10], immersive VR systems integrate users into an environment in which all real-world perception is blocked, so only computer-generated images are seen [10]. Similar to constraint-induced movement therapy (CIMT) [12, 13], and interactive video games [14], there is evidence that VR-wise interventions, which require repetitive and task-specific activities, could improve the restoration of upper limb function after stroke [15, 16]. Since VR is a type of interactive simulation combining computer hardware and software in which users can have close-to-reality experiences [17], it provides subjects with a more varied and realistic sensory perception experience and simulates the body movements of daily life, making rehabilitation more entertaining and involving for the subjects [18, 19].

Non-immersive VR systems have been widely used in stroke rehabilitation for several years, with the aim of improving motor function [6, 20]. Most of these studies have indicated that non-immersive VR-based rehabilitation is effective for upper limb functional improvement in individuals following stroke [21–24] but not significantly more beneficial compared with conventional rehabilitation, likely due to lack of relevant tasks provided by non-immersive VR [6]. Although it was reported that physical exercises through VR programs are effective for functional improvement in subjects with neurologic disorders [25] and that immersive VR systems may enhance motor learning and motor control [6], only one study has demonstrated that immersive VR-based rehabilitation can improve the effectiveness of fine hand-motion rehabilitation training [26]. However, what is the most appropriate frequency, intensity, and type of immersive VR-based rehabilitation to promote motor recovery and critical brain reorganization in this early post-stroke stage remains unknown. Functional magnetic resonance imaging (fMRI) has been important in exploring the neural mechanisms of recovery after brain disease, for instance, exploring patients’ motor execution networks post-stroke [27, 28]. Therefore, a longitudinal magnetic resonance image (MRI) study (similar to the ones performed previously in subjects with subacute back pain [29, 30]) will be implemented. Using MRI techniques, brain mechanisms related to strategies that enable the rehabilitation of repetitive, relevant, and skilled activities in the early stage post-stroke can be explored.

There are two reasons for choosing subjects with subacute stoke rather than other stages post-stroke in the clinic trial. First, in this subacute stage, patients have been shown to have the best and most rapid functional recovery [31], which benefits the observations of critical brain reorganization. Second, in China most stroke patients would be hospitalized during this stage, which makes recruitment and MRI scanning easier.

In summary, in this study we will use immersive VR training in post-stroke rehabilitation and assess the effectiveness in eliciting upper-limb motor recovery post-stroke compared to traditional rehabilitation training. Additionally, we will investigate the underlying brain mechanisms of immersive VR-based rehabilitation using MRI techniques.

## Methods/design

### Aim

The aim of the study is to assess the effectiveness of immersive VR-based upper extremity rehabilitation on patients with subacute stroke and explore the underlying brain mechanisms of immersive VR-based rehabilitation. The arm motor section of the Fugl-Meyer assessment (FMA) [32, 33] will be used to assess the effectiveness, and MRI techniques will be applied to investigate the brain mechanisms. The details will be discussed in the sections “Primary outcome measure” and “Secondary outcome measures”. It is presumed that motor learning and motor control is pivotal in the development of sensorimotor interventions for post-stroke recovery and that VR-based intervention may enhance motor learning and motor control [6].

### Study design

The Institutional Review Board of the Second Affiliated Hospital and Yuying’s Children Hospital, Wenzhou Medical University, China, approved this study. Prior to inclusion, all subjects will be informed about the objectives and procedures of the study. Subjects who meet the inclusion criteria must provide informed consent before entering into the study.

Subjects (*n* = 60) diagnosed with stoke in its subacute stage (defined as more than 1 week and less than 12 weeks after stroke onset) from an in-patient stroke rehabilitation unit in China will be enrolled in a single-blinded randomized controlled trial for 15 weeks. They will be randomized in a 1:1 fashion into (1) a new 3-week rehabilitation training program with an immersive VR system, (2) a 3-week conventional rehabilitation program. The random allocation will follow a covariate-adaptive randomization procedure [34, 35]. Each subject will be randomly assigned a code based on computer-generated, stratified, permuted block randomization with a block size of 8 and balanced by age and location of stroke.

All subjects will receive three assessments at the following time points: immediately following enrollment but before randomization (week 0), immediately following conclusion of the randomized rehabilitation program (week 3) and follow up 12 weeks after conclusion of the rehabilitation program (week 15). The assessment includes inclusion and exclusion of subjects, clinician-filled questionnaires and MRI scans. To avoid assessment bias, all inclusion and exclusion assessments and clinician-filled questionnaires will be completed by physiotherapists who are blinded to this study and with at least 2-years of experience in physical therapy. The flow chart for the study is shown in Fig. 1 and the schedule of enrollment, interventions, and assessments of the study (as recommended by Standard protocol items: recommendation for interventional trials (spirit) 2013 [36]) is shown in Fig. 2.

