### Sample size considerations

This randomized controlled trial is a two-group independent design examining the effects of immersive VR on rehabilitation of subjects with subacute stroke. We assumed a two-tailed comparison and set the type I error rate at 0.05 with 80% power. We plan to screen approximately 100 individuals with subacute stroke. After screening, 80 subjects will be recruited and randomized to the experimental group or the control group. As a conservative estimate (dropout rate = 25%), we presume that 60 subjects will complete the study. To reduce the dropout rate, we will employ two strategies to keep participants engaged: regular communication via phone or social media and clinician visits. After conducting a power analysis based on the aforementioned statistical parameters using the software GPower3.1.9.2 [39], the effect size is calculated as 0.74, which is between a medium (0.5) and large (0.8) effect size [40]. Moreover, there is evidence from a small sample (8 subjects) that VR-enhanced treadmill training for 5 sessions per week over 3 weeks induces significant cerebral reorganization [41]. Thus, 30 subjects for one group is sufficient to assess the effectiveness of immersive VR training in post-stroke rehabilitation in eliciting upper-limb motor recovery post-stroke compared to traditional rehabilitation training, and to investigate the underlying brain mechanisms of immersive VR-based rehabilitation using three MRI modalities.

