### Intervention design

Subjects in the control group will receive 60-min conventional rehabilitation training per day, 5 days per week for 3 weeks. This conventional rehabilitation delivered by a therapist at the hospital includes physical and occupational therapy (upper extremities flexion and extension training) which comprise task-related practice for gross movements and dexterity, including different grips and selective finger movements, strength training, stretching, and training in daily life activities. Conventional rehabilitation will be designed with similar intensity and complexity to simulate the skills required in the immersive VR group. Researchers in the study will supervise and encourage all participant to fully participate in the training to guarantee the quality of the training. In contrast, subjects in the experimental group will receive 30 min of conventional rehabilitation and 30 min of immersive VR rehabilitation training per day, 5 days per week for 3 weeks conducted by a therapist at the hospital. The details will be discussed in the section “VR training protocol”.

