## Discussion

This clinical trial aims to evaluate the effectiveness of immersive VR-based rehabilitation in upper-limb motor recovery post-stroke compared to traditional rehabilitation through questionnaires and evaluation of brain mechanisms via MRI. Previous studies have shown that non-immersive VR is safe but not significantly more beneficial compared with conventional rehabilitation [6]. It was suggested, however, that immersive VR systems may have more beneficial results in improving the patient’s upper extremity motor function and quality of life after stroke, as these VR system programs provide a combination of extra spatial transformation of uncoupled eye–hand movements, enhanced motion control, and more entertainment for patients, thereby motivating motion learning [6]. The results of this study will provide evidence to either support or not support this hypothesis.

To avoid creating an imbalance between the two groups in rehabilitation time, which may introduce additional variables to explain the resultant improvement in upper extremity motor function, the total rehabilitation time is set to be identical for the two groups. Moreover, in order to observe the long-term outcomes of immersive VR-based rehabilitation in terms of upper limb motor function, the trial will follow up all subjects 12 weeks after they have finished rehabilitation.

The main limitation in this trial is its single-center design and the limited sample size. There is clearly a need for multicenter, large-scale trials to determine the benefits of immersive VR-based rehabilitation, but before launching these it is important to demonstrate feasibility and effectiveness. Another limitation is that current immersive VR technology is still unable to simulate all rehabilitation training. As a compromise, the subjects in the experimental group will experience a combination of 30-min normal rehabilitation and 30-min immersive VR rehabilitation.

In conclusion, this study aims to explore the immediate and longer-term effects of immersive VR-based rehabilitation in subjects in the early stage of stroke, and to discuss the mechanism of its impact on the brain’s anatomical and functional reorganization. The results of the trial will be of benefit to future patients with stroke and may provide a new and better method of stroke rehabilitation.

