## Trial status

Subject recruitment is underway.

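### The allocation is described in two ways that need reconciling, and the analysis adjusts for the balancing factors (age, stroke location) only if they turn out imbalanced

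*Protocol article*

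**What the plan says.** All places are in the protocol article.

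- **Study design**, first sentence on method: "The random allocation will follow a covariate-adaptive randomization procedure [34, 35]".
- **Study design**, next sentence: codes come from "computer-generated, stratified, permuted block randomization with a block size of 8 and balanced by age and location of stroke". The ratio is equal: "They will be randomized in a 1:1 fashion". No imbalance measure, biased-coin probability or linking sentence is given. Neither are age cut-points or location categories.
- **Statistical analysis**: the arms are compared by two-way repeated measures ANOVA. Analysis of covariance is added only when a demographic or clinical characteristic differs significantly between arms.
- **Blinding and setting**: "clinician-filled questionnaires will be completed by physiotherapists who are blinded to this study". The same physiotherapists assess eligibility. On training: "Researchers in the study will supervise and encourage all participant to fully participate in the training". The Discussion acknowledges the single centre: "The main limitation in this trial is its single-center design and the limited sample size".
- **Trial status**: "Subject recruitment is underway".

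**The concern.** Covariate-adaptive allocation, such as minimisation, usually means that each assignment depends on the covariates and assignments of earlier subjects. Stratified permuted blocks are lists prepared in advance within strata. A reader cannot tell which one generates the sequence.

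The larger statistical matter follows from the balancing itself. Both methods force the arms to be alike on age and stroke location, which makes the estimated treatment difference less variable. An analysis that omits those factors still counts their variation as noise, so its standard error does not reflect the precision the design achieved. A rule that adjusts only after a significant imbalance leaves out the very factors that the design has balanced.

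The third matter is concealment. A single block size became public while subjects were still being allocated in one unit, where those delivering treatment necessarily know which treatment it is.

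**Working it through.** **1. The plan's own figure.** Sample size considerations: "We assumed a two-tailed comparison and set the type I error rate at 0.05 with 80% power". With 30 completers per group, the two-sample t test (noncentral t) gives a detectable standardised effect of 0.736, which rounds to the stated 0.74. Also 60/(1 − 0.25) = 80 randomised, as stated. Nothing below disturbs these figures.

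**2. Will the imbalance rule fire for the balancing factors?** Within a stratum, blocks of 8 cannot leave a difference above 4. The number of strata is not given. Assume two age groups by two locations, with 80 randomised and 20 per stratum. The worst case for age is both younger strata at +4 and both older strata at −4, that is 24 v 16 and 16 v 24:

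chi-square = 80 × (24×24 − 16×16)² / (40×40×40×40) = 80 × 320² / 2,560,000 = 3.2, p = 0.074.

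In this layout even the worst case misses 0.05. With other stratum sizes, or with age tested as a continuous variable, the rule could fire, but balancing makes that less likely than under simple randomisation.

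**3. Cost of leaving the factors out.** Let R² be the share of outcome variance that the factors explain. It is not in the documents, so 0.05 to 0.20 is an assumption. Assume also close balance, 30 per group, and 0.74 measured against the total standard deviation. In normal approximation:

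- λ = 0.74 / √(2/30) = 2.866; power with R² = 0 is Φ(2.866 − 1.960) = 81.8% (80.5% by the t test).
- Unadjusted standard error is too large by the factor 1/√(1 − R²).
- True type I error, unadjusted: 2 × [1 − Φ(1.960/√(1 − R²))].
- Power, unadjusted: Φ((λ − 1.960)/√(1 − R²)).
- Power, adjusted: Φ(λ/√(1 − R²) − 1.960).

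| R² | SE too large by | True type I error | Power unadjusted | Power adjusted |
|---|---|---|---|---|
| 0.05 | 2.6% | 4.4% | 82.4% | 83.7% |
| 0.10 | 5.4% | 3.9% | 83.0% | 85.6% |
| 0.20 | 11.8% | 2.8% | 84.4% | 89.3% |

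The error is on the conservative side: the test is too cautious and gives up about 1 to 5 points of power.

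In a repeated measures model, R² is the share explained of the contrast being tested. For the group main effect this concerns the mean over visits. For a group-by-time interaction it concerns change, so the factors matter there only if they predict change, and they must be crossed with time to have any effect.

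**4. Predictability.** In a complete block of b = 2m, the final run of identical assignments has mean length 2m/(m + 1), and the share known with certainty is 1/(m + 1). This requires knowledge of the block size, the stratum and all earlier allocations in it.

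| Block size | Certain | Best guess right |
|---|---|---|
| 4 | 1/3 = 33.3% | 70.8% |
| 6 | 1/4 = 25.0% | 68.3% |
| 8 | 1/5 = 20.0% (1.6 of 8) | 66.6% |

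An unpredictable sequence gives 50% for the best guess. Of these sizes, 8 is the least predictable, so shorter blocks alone would make matters worse.

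**The case against.** Some authors use covariate-adaptive as a broad term that includes stratified blocks. The second sentence may then simply specify the first, and only one operational procedure is actually described. The two cited references could settle this but are not at hand. This stands: the documents do not show two incompatible procedures in operation, and reconciling the sentences is mainly editorial.

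Covariates are often left to an analysis plan, which is not shown. This stands only in part. The article does not stay silent; it fixes a conditional rule, and that rule is the problem.

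On concealment, eligibility is assessed by blinded physiotherapists. Nothing says that the researchers who supervise training enrol subjects or keep allocation records by stratum. Central concealment may be described in the full protocol. All of this limits the point, and a reader who inferred that selective enrolment was likely would go beyond the text.

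A reader might also infer that a fixed block size of 8 spoils balance, or that trouble arises because 60 is not a multiple of 8. The documents do not support either. Sample size considerations randomises 80, although Study design says 60, and blocks fill within strata, so overall divisibility says little. In simulations with 80 subjects and 4 to 8 assumed equal strata, the mean arm difference is 1.8 to 2.6 subjects, against 7.1 for simple randomisation. Varying the size does not in itself improve this: with 60 subjects and 8 strata the mean is 2.6 for fixed 8, 2.4 for mixed 4/6/8 and 2.8 for mixed 6/8/10. At an effect of 0.74, power by the t test is still 80.0% with a 33/27 split.

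**Conclusion.** The point holds in three parts of unequal weight.

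- **Analysis (main part).** Conditional adjustment will usually omit the factors that the randomisation balances. Validity against false positives is not threatened. The loss is a standard error 2.6% to 11.8% too large and about 1 to 5 points of power, if the factors explain an assumed 5% to 20% of the variance of the tested contrast. If they explain nothing, the loss is nil.
- **Description.** The two sentences need to be made one. This is a clarification, not evidence that allocation was done wrongly.
- **Concealment (secondary).** With the published size, 20% of allocations in complete blocks are certain to someone who tracks every stratum. The risk is real but limited by blinded eligibility assessment and by safeguards that may stand in documents not shown.

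No conclusion about poor balance between the arms follows.

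**What to change.** 1. State in Study design the one procedure in use, so that the term and the specification agree. This is a text correction.
2. In the primary model for the Fugl-Meyer arm score, include age and stroke location as prespecified covariates regardless of observed imbalance, crossed with time if the tested effect is a group-by-time contrast. Remove the significance trigger for these two factors. Both are already needed for allocation, so the change costs no data collection and only a few degrees of freedom. Make it before outcome data are examined by arm.
3. For allocations not yet issued, generate the remaining list with varying block sizes, not merely shorter ones, withheld from site staff and held by someone independent of treatment. The cost is regenerating the unissued part; subjects already allocated are unaffected.

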**Fig. 1 Fig1:**
[figure not shown]
Chart of study flow. REDCap, Research electronic data capture; T1-MRI, high-resolution anatomical magnetic resonance imaging; RS-fMRI, resting-state functional magnetic resonance imaging; DTI, diffusion tensor imaging; VR, virtual reality

